## Methods

### Design

The Thrive program will be evaluated in an RCT with 2 conditions and 4 measurement occasions. Thus, there will be two main independent variables—one between-group factor and one repeated-measure factor—as well as a selection of covariates and dependent variables. The two conditions will be the intervention (ie, the Thrive webinar program) and an active control condition (only an abbreviated pamphlet version of the educational components of the program). The study will take place over a 12-week period, and a web-based survey will be administered at each of the 4 measurement occasions. In week 0 (ie, 1 week before the program commences), the participants will complete the baseline survey (before the intervention). The Thrive program (and the parallel active control program) will run for 7 weeks, from week 1 to week 7. The participants will complete the second survey in week 4 (at the midpoint of the program), the third survey (after the intervention) in week 8 (ie, 1 week after the conclusion of the program), and the fourth survey (follow-up) in week 12 (ie, 4 weeks after the intervention). Each survey will take approximately 20 to 30 minutes to complete. Once all 4 surveys have been administered and the study period has concluded, all the participants in the active control condition will be given access to the full version of the Thrive program. The study timeline is illustrated in Figure 1.

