### Sample Size

Power calculations suggest that at least 200 participants need to be recruited (100 per condition) to detect a small group-by-time interaction effect at 80% power. This sample size was calculated using the statistical software package G*Power (version 3.1.9.2) [32,33]. Assuming a small effect of 0.01 (partial *η*^2^), a conventional type-1 error rate of 0.05, and a correlation of 0.5 among the repeated outcome measures, the study will be able to detect such an effect at 80% power with 69 participants in each group. However, considering an attrition rate of up to 30% by the final measurement occasion, it will be necessary to recruit at least 99 people per group, so we will aim for a total sample size of at least 200. The projected attrition rate of 30% is based on the attrition rates reported in previous RCTs [23-25] that examined interventions to increase well-being in hospital staff. Additional power calculations show that the study will be able to detect effects as small as 0.04 (partial *η*^2^) even under the strictest nonsphericity correction and possible attrition of up to 65%.

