### Primary and Secondary Outcomes

The primary outcomes for this RCT will be the participants’ levels of well-being (as measured by the COMPAS-W) and their levels of psychological distress (as measured by the Depression, Anxiety, and Stress Scale–21-item version). Thus, the primary outcomes will encompass both dimensions of mental health: mental well-being and mental illness. The secondary outcomes will be health and lifestyle habits, mood states, compassion (for oneself and others), mindfulness, work performance, and work engagement. Program attendance, resiliency resources, medical history, trauma, coping styles, and pandemic-related variables will serve as potential moderator variables along with demographic variables such as age, sex, ward, and occupation. The primary end point for the analysis will be the third measurement occasion (week 8), and the secondary end points will be the second and fourth occasions (week 4 and week 12).

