### Analysis

Missing values in the data set will be estimated via multiple imputation, and the initial analyses will be conducted on an intention-to-treat basis followed by per-protocol analyses to account for levels of treatment compliance (eg, program attendance). The data will be analyzed via a linear mixed model that will allow the group-by-time interaction effects to be estimated. It is hypothesized that levels of well-being will increase over time in the intervention condition relative to the active control condition. Similarly, it is hypothesized that levels of psychological distress (ie, symptoms of depression, anxiety, and stress) will decrease over time in the intervention condition relative to the active control condition. There may also be a group-by-time interaction effect on one or more of the secondary outcomes. For example, the intervention may promote increased compassion, mindfulness, or work engagement. Furthermore, any interaction effect may itself be moderated by a variable such as resilience or coping style (cf [9,31]).

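### The primary end point is week 8, but the sample size is for a four-occasion interaction and the analysis text does not tie its interaction effects to week 8

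*Protocol article*

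**What the plan says.** - **End point** (Primary and Secondary Outcomes): "The primary end point for the analysis will be the third measurement occasion (week 8"). Weeks 4 and 12 are ranked as secondary.
- **Analysis** (Analysis): "The data will be analyzed via a linear mixed model that will allow the group-by-time interaction effects to be estimated". The well-being hypothesis is that "levels of well-being will increase over time in the intervention condition relative to the active control condition", and the distress hypothesis is its mirror image. Neither names a visit.
- **Design** (Design): "The Thrive program will be evaluated in an RCT with 2 conditions and 4 measurement occasions". The main independent variables are "one between-group factor and one repeated-measure factor", alongside covariates that are not specified there. The week-0 survey is one of the four occasions: "the participants will complete the baseline survey (before the intervention").
- **Sizing** (Sample Size): the target is "to detect a small group-by-time interaction effect at 80% power". The inputs are given as "Assuming a small effect of 0.01 (partial *η*^2^), a conventional type-1 error rate of 0.05, and a correlation of 0.5 among the repeated outcome measures". From these it obtains 69 per group, raised to 99 for 30% loss by the last occasion and rounded to 200 in total.

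The article does not state the degrees of freedom, call the test omnibus, say how time is coded, or say how baseline enters the model.

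**The concern.** A single declared visit calls for a single between-arm contrast at that visit. An interaction over four occasions is a different quantity. It asks whether the between-arm gap varies at all across weeks 0, 4, 8 and 12, and its F-test has no direction, whereas the hypotheses do.

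Two things are at stake. First, a reader will take 80% as the power for the declared end point, and it is power for something else. Second, if it stays open whether the multi-df interaction or the week-8 contrast decides the trial, the two can disagree and the choice can be made after the results are seen.

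Baseline handling matters for the same contrast. If baseline is simply one level of the repeated factor with free arm means, the week-8 interaction contrast is a difference in change scores. At the protocol's own correlation of 0.5, that is no more precise than ignoring baseline.

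**Working it through.** **Inputs from Sample Size:** partial eta-squared 0.01, so f² = 0.01/0.99 = 0.0101 and f = 0.1005; alpha 0.05; correlation ρ = 0.5; 69 completers per group (N = 138). Design gives 2 groups and m = 4 occasions.

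**1. Reproduce the stated figure.** For a within-between interaction, the noncentrality is λ = f²·N·m/(1−ρ), with df1 = m−1 and df2 = (N−2)(m−1). For m = 4 and N = 138, λ = 0.0101 × 138 × 4/0.5 = 11.15, with df 3 and 408.

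| Occasions in the test | df1 | Completers per group for 80% | Power at that N |
|---|---|---|---|
| 4 (weeks 0, 4, 8, 12) | 3 | 69 | 80.6% |
| 3 | 2 | 81 | 80.4% |
| 2 (weeks 0 and 8) | 1 | 99 | 80.4% |

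Only the four-occasion calculation gives 69; with 68 per group, power is 79.9%. The inflation 69/0.7 = 98.6, hence 99, also reproduces. The section's further statement on an effect of 0.04 involves a sphericity correction, which has meaning only for a test with more than 1 df.

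**2. An interaction without a week-8 effect.** With between-arm gaps D_t (in SD) at the four occasions, f² = mean over t of [(D_t − D̄)/2]². A gap at week 4 only, or at week 12 only, of 0.46 SD gives f² = 0.0101. The 3-df test then has the same 80.6% power although the week-8 gap is zero.

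**3. Power at week 8, 69 per arm.** This is a two-sided t-test with SE = √(2v/69). For the unadjusted change from baseline, v = 2(1−ρ) = 1.00. With baseline as covariate, v = 1−ρ² = 0.75.

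(a) *0.01 read as the week-0/week-8 interaction.* Here D = (0, d), so f² = d²/16 and d = 4 × 0.1005 = 0.402 SD. Power is 65% unadjusted and 77% adjusted. Reaching 80% needs 99 and 74 completers per arm respectively.

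(b) *0.01 kept as the four-occasion effect.* The week-8 gap then depends on the time profile. The profiles below are assumptions, not document figures.

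| Profile at weeks 0, 4, 8, 12 | Week-8 gap (SD) | Unadjusted | Baseline-adjusted |
|---|---|---|---|
| Linear growth (0, 1/3, 2/3, 1) | 0.36 | 55% | 68% |
| Step (0, 1, 1, 1) | 0.46 | 77% | 88% |
| Ramp to plateau (0, 0.5, 1, 1) | 0.49 | 81% | 90% |
| Peak at week 8 (0, 0.5, 1, 0.5) | 0.57 | 91% | 97% |

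**4. Detectable week-8 difference at 80% power, 69 per arm:** 0.48 SD unadjusted and 0.42 SD adjusted.

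**5. Gain from adjustment at other correlations.** The variance ratio is (1−ρ²)/[2(1−ρ)] = (1+ρ)/2. That is 0.75 at ρ = 0.5 (25% less variance) and 0.90 at ρ = 0.8 (10% less).

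**The case against.** The strongest reply is that the 3-df test is back-calculated from the sample size, and a sizing shortcut does not fix the analysis. The Analysis section speaks of interaction effects, in the plural, being estimated. A mixed model with categorical time gives signed contrasts at each visit, and the outcomes section ranks the visits. Read together, these are compatible with a week-8 contrast as the primary test. Time coding and baseline handling may properly sit in a full protocol or SAP that is not shown, and the Design section does allow for covariates.

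Most of this stands. A reader might infer that the planned analysis cannot answer the week-8 question, or that it throws the baseline away. The article supports neither. The model described can supply the week-8 contrast. The efficiency loss arises only if the arm means at baseline are left free and baseline is not a covariate, and it shrinks as the correlation rises.

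A reader might also infer that the trial is underpowered. That is not shown either. Step and ramp profiles give 77% to 81% even unadjusted. The lowest figure needs benefit to keep growing to week 12, although the program ends in week 7. Moreover, 69 per arm allows for loss by the final occasion. If the 30% accrued evenly over 12 weeks (an assumption), loss by week 8 would be 20%, leaving about 80 of 100 per arm. The unadjusted powers in (b) would then be 62%, 83%, 86% and 95%.

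What the reply does not remove is the mismatch in the stated text. The end point, the hypotheses and the sizing target are all given here. A later contrast chosen in a SAP would still leave Sample Size quoting power for a different test.

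**Conclusion.** The point holds as a lack of alignment. Week 8 is the declared primary end point, the sample size is for a four-occasion interaction including baseline, and the analysis text does not link its interaction effects to week 8. The quoted 80% is therefore not power for the declared end point. The article's own figures do not determine that power: unadjusted, at 69 per arm, it is 65% under reading (a) and 55% to 91% under reading (b).

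The reproduction of 69 is exact. Confidence in the point as a whole is moderate, because treating the 3-df interaction as the headline test is an inference from the Design and Sample Size sections. The risk of significance through week 4 or week 12 alone applies only if that test is the decisive one. The power figures rest on ρ = 0.5, equal variances across occasions and, in (b), the assumed profiles.

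**What to change.** In the Analysis section, name as the primary test the 1-df between-arm difference at week 8 from the linear mixed model. Use either the baseline score (with its interaction with time) as covariate for weeks 4, 8 and 12, or a model with a common baseline mean across arms. Report weeks 4 and 12 as secondary contrasts from the same model and the omnibus interaction as supportive.

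In Sample Size, state power or the detectable difference for that week-8 contrast, with the assumed correlation and the number expected at week 8.

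The cost is a few sentences of analysis text and one restated power sentence. No new data are needed, since baseline is already collected.

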### Anonymity and Confidentiality

Although each participant will provide their name, email address, and ward to enroll in the Thrive program, their survey responses will be completely anonymous and linked via a participant code number. At each measurement occasion, the participants will be emailed a link to the survey and, when they click on the link, they will be taken to the web-based Qualtrics (Qualtrics International Inc) platform that will be hosting the surveys. The web-based surveys will not ask for any information that could be used to identify any individual participant, and Qualtrics will not record any metadata from the respondents either. To match each participant’s responses on one measurement occasion with their responses on the other occasions, each survey will ask the respondent to provide a self-generated code. The respondent will be instructed to take the last 3 digits of their mobile phone number and the last 2 digits of their birth year to create their own 5-digit code. For example, if a participant’s phone number ended in the digits *123* and they were born in 1970, their code would be *12370*. One might argue that someone familiar with a given participant could identify their survey responses from this code, but none of the researchers who will have access to the raw data will be personally acquainted with any of the participants. Furthermore, once all the data have been collected and all the responses have been matched, the 5-digit codes will be deleted from the data set and replaced with generic, arbitrary ID numbers.

At each measurement occasion, the survey link sent to the intervention participants will be different from the link sent to the active control participants (even though the surveys themselves will be identical). This will allow the researchers to keep track of which condition each participant is in without relying on self-reports.

### Data Storage and Security

Once the data have been collected via Qualtrics, they will be downloaded directly from the Qualtrics servers onto the secure internal server at NeuRA. Only the research team will have access to the data. There will be no intermediaries (either human or technological) between Qualtrics and the research team.

### Analysis

Missing values in the data set will be estimated via multiple imputation, and the initial analyses will be conducted on an intention-to-treat basis followed by per-protocol analyses to account for levels of treatment compliance (eg, program attendance). The data will be analyzed via a linear mixed model that will allow the group-by-time interaction effects to be estimated. It is hypothesized that levels of well-being will increase over time in the intervention condition relative to the active control condition. Similarly, it is hypothesized that levels of psychological distress (ie, symptoms of depression, anxiety, and stress) will decrease over time in the intervention condition relative to the active control condition. There may also be a group-by-time interaction effect on one or more of the secondary outcomes. For example, the intervention may promote increased compassion, mindfulness, or work engagement. Furthermore, any interaction effect may itself be moderated by a variable such as resilience or coping style (cf [9,31]).

### Publication Policy

The results of this study will be shared with the hospital, the funding body, the overseeing organizations, and other relevant stakeholders. The results will also be published in peer-reviewed scholarly journals, presented at academic conferences, and publicized on the media platforms used by NeuRA and UNSW. In all publications and presentations of the findings, the data will be presented in aggregate, and no individual participants will be identifiable.

### Ethics Approval

This study has received ethical approval from the Human Research Ethics Committee of the South Eastern Sydney Local Health District (approval granted on November 9, 2020; project 2020/ETH02090), and this approval was ratified by the UNSW Human Research Ethics Committee on November 12, 2020.

## Results

The trial has been prospectively registered with the Australian New Zealand Clinical Trials Registry (registration approved on January 14, 2021; trial ID ACTRN12621000027819).

The Thrive program was developed between August 2020 and January 2021. For logistical reasons, it was decided that the program would be implemented incrementally throughout the hospital. The hospital comprises >50 wards, of which 5 were selected for the initial wave of recruitment, which occurred in December 2020 and January 2021. For the resulting cohort of participants, survey 1 was administered in February 2021, survey 2 was administered in March 2021, survey 3 was administered in April 2021, and survey 4 was administered in May 2021. The participants in the active control condition were provided with the full version of the program between May 2021 and July 2021. CPD points and certificates were awarded in August 2021. Since the successful administration of the Thrive program in the initial selection of wards, the research team and hospital management have decided to continue rolling out the program, and the staff from the remaining wards will be invited to participate in the trial from October 2021 to December 2021.

## Discussion

This study contributes to the field of research on mental well-being in a number of important ways. It addresses a population—health care workers—whose occupations entail relatively high levels of stress and burnout and who may therefore especially benefit from a staff well-being program such as Thrive. This consideration is particularly salient in light of the COVID-19 pandemic, which has confronted health care workers with additional demands and dangers. This study also addresses the methodological shortcomings of previous RCTs of interventions for health care workers with a relatively large sample, stratified random allocation, and an active control condition.

This study will furnish an evidence base for the role of a comprehensive, neuroscience-based psychoeducational program in preserving or enhancing mental well-being in health care workers. The results of the trial will be used to evaluate and refine the Thrive program so that it may be implemented effectively not only at the target hospital but also at other hospitals and potentially other settings such as corporate workplaces or educational institutions.

This trial will also contribute to the knowledge base on well-being promotion more broadly. The 21st century has seen an evolution in the understanding of mental health, revealing that a lack of illness is not enough—one also needs sufficient well-being to flourish. The Thrive program represents an attempt at putting this understanding into practice, informed by a measure of well-being—the COMPAS-W—that has been validated in terms of not only behavioral outcomes but also neural and genetic markers. It is hoped that this line of research will lead to substantial advancements in our ability to promote greater well-being—and, thus, greater mental health overall—in health care workers and beyond.

## Appendix

Multimedia Appendix 1 Daily Life Events scale, COVID-19 Exposure Survey, and Thrive Program Attendance and Satisfaction Survey.

## Abbreviations

COMPAS-W: Composure, Own-worth, Mastery, Positivity, Achievement, and Satisfaction for Wellbeing Scale
CPD: Continuing Professional Development
DLE: Daily Life Events
NeuRA: Neuroscience Research Australia
POWH: Prince of Wales Hospital
RCT: randomized controlled trial
UNSW: University of New South Wales
